#### V-1-1. Unvaccinated elderly and high COVID-age population:

1. SARS-CoV-2 RNA detected in a specimen, or positive antigenic test,  $\leq 7$  days after onset of symptoms
2. Symptoms of COVID-19 (so including but not limited to: fever; cough; breathlessness; chest pain; wheeze; sore throat; haemoptysis; runny nose; fatigue; muscle or joint pain; confusion; headache; seizures; nausea; vomiting; diarrhoea; abdominal pain; poor appetite; skin ulcers or rash; ear pain; conjunctivitis; anosmia; bleeding; lymphadenopathy). The attending clinician will determine if symptoms are consistent with COVID-19.
3. Clinical status not requiring admission to hospital for COVID-19 disease and oxygen support
4. Ability to transfuse (per randomisation) within 7 days after onset of symptoms
5. Men or women, 70 years or older  
OR  
under 70 years with significant comorbidities (arterial hypertension, diabetes, obesity, asthma or other chronic pulmonary disease, cardiovascular disease, cerebrovascular disease, chronic kidney disease / dialysis, liver disease, chronic neurological disease, rheumatoid arthritis, lupus or psoriasis) resulting in a 'COVID-age' of 70 years or more according to the ALAMA risk calculator <https://alama.org.uk/covid-19-medical-risk-assessment/>
6. Signed written informed consent

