**X-1-2. Intention to treat population**

The analyses will be performed according to the intention-to-treat (ITT) principle. The ITT population (by patient cohort) will be used for all efficacy analyses. This will consist of all randomised patients according to their allocated arm irrespective of whether the patient actually received study drug or the patient's compliance with the study protocol, in the treatment group assigned by the randomization.

The list of protocol deviations will be established and the reasons for non-evaluable cases will be indicated as following:

- Inclusion criteria not satisfied.
- Deviations related to the study drug administration

All randomized patients will be included in the primary ITT efficacy analysis.

A modified intention to treat population (mITT) will be considered. The modified ITT population will exclude ineligible patients who were randomized in error.

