### **X-2. Sample size determination**

The Sample size of the study is based on the risk of severe COVID-19 and the effect previously observed by Libster et al. in an elderly high-risk population and a similar intervention of early convalescent plasma. In this study, 31% of the control group patients experienced severe COVID-19 disease, the relative risk of severe COVID-19 in treated patients was 0.52 (95% Confidence Interval 0.29–0.94). We estimate that the risk of severe COVID-19 in the elderly population will be 30% and the relative risk reduction in the treated group will be 0,5.

For a cohort, group sample sizes of 158 in group 1 and 158 in group 2 achieve 90% power to detect a difference between the group proportions of -0.15. The proportion in group 1 (the treatment group) is assumed to be 0,30 under the null hypothesis and 0.15 under the alternative hypothesis. The proportion in group 2 (the control group) is 0.30. The test statistic used is the two-sided Z-Test. The significance level of the test is 0.05. The sample size is increased to 170 to account for missing data/loss to follow up.

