#### **Handling of missing or incoherent data**

In the case outcomes would be missing, binary missing outcomes will be treated as treatment failures in interim and primary final analyses, with an imputation by last value carried forward as a sensitivity analysis. For time-to-event outcomes, they will be naturally handled using methods for censored data. No imputation will be used for secondary efficacy and safety outcomes.

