#### **Primary endpoint analysis**

Primary endpoint definition: the proportion of patients with (1) at least one overnight stay in hospital for progressive COVID-19 symptoms, or (2) who died by day 28 after randomisation.

The primary outcome will be analysed using a two-sided Z-test to compare proportions of events in the randomisation groups. The risk difference will be provided with its 95% confidence interval. As a sensitivity analysis accounting for stratification on the centre, the endpoint will be analysed using a generalized linear mixed models (with logit link) with a random centre effect. Adjustment for major prognostic factors will be considered depending on the evolution of medical knowledge on the prognosis of patients infected by SARS-Cov-2.

Chen et al. have shown that if one increases the sample size only when the interim result is promising, the type-1 error is not inflated by use of the conventional Wald statistic. The significance level of the primary analysis will therefore remain at 0.05.

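### Last value carried forward is a weak check on missing primary outcomes: it cannot show whether the conclusion depends on missing patients' outcomes differing by arm

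*Protocol*

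**What the plan says.** Protocol X-3 (Handling of missing or incoherent data) gives the primary rule: "binary missing outcomes will be treated as treatment failures in interim and primary final analyses". The only check on that rule comes in the same sentence: "with an imputation by last value carried forward as a sensitivity analysis". X-6 repeats the same rule and adds nothing.

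The primary endpoint is cumulative: at least one overnight stay for progressive COVID-19 symptoms, "or (2) who died by day 28 after randomisation". Both cohorts share an entry criterion (V-1-1 and V-1-2): "Clinical status not requiring admission to hospital for COVID-19 disease and oxygen support". All randomised patients stay in the primary analysis (X-1-2), and "The primary outcome will be analysed using a two-sided Z-test to compare proportions of events in the randomisation groups".

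The protocol names two other secondary looks at the primary result, and neither concerns missing data. The mixed model is introduced with "As a sensitivity analysis accounting for stratification on the centre". As for the second population, "The modified ITT population will exclude ineligible patients who were randomized in error".

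On expected loss, X-2 takes 158 per arm and says: "The sample size is increased to 170 to account for missing data/loss to follow up". Sections I and IV-2 describe the allowance as 5% additional patients.

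**The concern.** A sensitivity analysis for missing data should change the assumption about the missing patients in a way that could overturn the result. Here a patient known to have been admitted or to have died is not missing. Anyone else lost before day 28, even on day 2, was event-free when last seen. Carrying the last value forward therefore amounts to coding missing as no event in both arms. The primary rule codes missing as event in both arms. Both analyses treat the arms identically.

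The trial is open-label without placebo. Plasma patients attend for transfusion and are observed afterwards, while control patients may be sampled at home or sample themselves (VI-3, VII-4). Reasons for losing contact, and the outcomes behind them, could differ by arm. If losses are similar in number, the check returns the primary risk difference unchanged with a smaller standard error. A report could then call the result robust to missing data when the assumption that matters was never varied.

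**Working it through.** **The plan's own figure.** Event rates 0.30 and 0.15, two-sided alpha 0.05, power 90% (X-2), unpooled Z formula: (1.960 + 1.2816)² × (0.30×0.70 + 0.15×0.85) / 0.15² = 157.6, so 158 per arm. This reproduces. Going from 158 to 170 leaves 12 of 170 missing per arm (7.1%).

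**Identity.** Let e be observed events and m missing patients, each as a proportion of all randomised in the arm (T plasma, C control).
- Missing as failure: RD = (eT + mT) − (eC + mC)
- Last value carried forward: RD = eT − eC
- Difference: mT − mC

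With equal loss the difference is zero, whatever happened to the missing patients.

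**Illustration at the plan's rates.** 170 per arm, 12 missing per arm. Observed events are assumed to be 24 and 47, about 15% and 30% of 158. P-values are from the pooled two-sided Z-test.

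| Coding of missing patients | Plasma | Control | RD | p |
|---|---|---|---|---|
| All events (primary rule) | 36/170 | 59/170 | −0.135 | 0.005 |
| All event-free (last value) | 24/170 | 47/170 | −0.135 | 0.002 |
| Plasma 50%, control 25% | 30/170 | 50/170 | −0.118 | 0.01 |
| Plasma 8 of 12, control none | 32/170 | 47/170 | −0.088 | 0.054 |
| Plasma all, control none | 36/170 | 47/170 | −0.065 (95% CI −0.156 to +0.026) | 0.16 |
| Plasma none, control all | 24/170 | 59/170 | −0.206 | <0.001 |

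The first two rows are the planned pair. Seven plasma events and no control events among the missing would still give p=0.039, so with event-free missing controls the result tips at eight.

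**Unequal loss.** With 17 plasma and 7 control patients missing and the same observed events, the primary rule gives 41/170 − 54/170 = −0.076 and last value gives −0.135. The shift of 0.059 is (17 − 7)/170. The pair does detect this.

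**Smaller loss.** Five per cent of 170 is 8.5.
- With 8 missing per arm (24 of 162 and 49 of 162 observed events), the most adverse assignment is 32/170 vs 49/170: RD −0.100, p=0.03.
- With 9 missing per arm (24 and 48 observed), it is 33/170 vs 48/170: RD −0.088, p=0.056.

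**The case against.** The protocol promises a more detailed statistical analysis plan, and a tipping-point grid is ordinary content for it. That would be decisive if the protocol were silent. It is not: it selects the method, in two places, and the method chosen cannot do the job.

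Last value is not defined for this endpoint. Admissions are adjudicated by a panel, and one that could not be classified might be carried forward as an event. A reader might infer that every missing patient is coded event-free. The text does not go that far, and the identity then holds for the remaining missing patients only.

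A reader might also infer that the pair says nothing about missingness. That is too strong. It reveals unequal loss, and it brackets the case in which one coding applies to both arms.

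Loss may be small. VI-4-2 collects follow-up regardless of treatment completion, using medical notes, routine healthcare systems and registries, and VII-9 separates stopping treatment from withdrawing from follow-up. This reduces the likely size of the problem but does not change what the check can detect.

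Finally, one can choose observed counts close to p=0.05 so that a moderate difference between arms removes significance. At the plan's own rates, 50% versus 25% risk among the missing leaves p=0.01. The documents do not support saying that a positive result would be fragile in general.

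**Conclusion.** The point holds in a limited form. For the day-28 endpoint, the planned pair varies the coding of missing patients only in the same direction in both arms, so it cannot show dependence on outcomes that differ by arm.

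At the plan's rates with 12 of 170 missing per arm, that unexamined range is −0.065 to −0.206 around a reported −0.135. Significance is lost only under adverse assumptions, such as 8 of 12 missing plasma patients and no missing controls having events. With 8 missing per arm it is not lost at all; with 9, only the most extreme assignment crosses 0.05.

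The event counts are illustrative, and the event-free reading of last value is inferred from the endpoint and the entry criteria. A reader might take this as a case against counting missing outcomes as failures in the primary analysis. It is not: that rule, the test and the sample size are unaffected.

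**What to change.** In X-3 and X-6, for the primary endpoint, replace last value carried forward with a tipping-point analysis. It should vary the event probability of missing patients from 0 to 1 separately in each arm and report where the conclusion changes. State how a recorded but unadjudicated admission is coded.

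Multiple imputation by arm, from baseline and observed follow-up, may be added as a reference. It assumes outcomes are missing at random and so does not by itself answer the concern.

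The cost is a short text change in two places and a little more programming. No new data are needed.

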#### **Statistical software**

The analyses will be carried out using the R software version 4.0.5 or later (The R Foundation for Statistical Computing, Vienna, Austria) and SAS version 9.4 or later (SAS Institute Cary, NC).

#### **Characteristics at inclusion**

The characteristics of patients collected at inclusion will be described globally and by randomization group, using means, standard deviations, medians, interquartile intervals, minimum and maximum for quantitative variables and by their numbers and percentages by modality for qualitative variables. The number of missing data for each variable will also be reported. No statistical tests for comparison between groups will be carried out.

#### **Primary endpoint analysis**

Primary endpoint definition: the proportion of patients with (1) at least one overnight stay in hospital for progressive COVID-19 symptoms, or (2) who died by day 28 after randomisation.

The primary outcome will be analysed using a two-sided Z-test to compare proportions of events in the randomisation groups. The risk difference will be provided with its 95% confidence interval. As a sensitivity analysis accounting for stratification on the centre, the endpoint will be analysed using a generalized linear mixed models (with logit link) with a random centre effect. Adjustment for major prognostic factors will be considered depending on the evolution of medical knowledge on the prognosis of patients infected by SARS-Cov-2.

Chen et al. have shown that if one increases the sample size only when the interim result is promising, the type-1 error is not inflated by use of the conventional Wald statistic. The significance level of the primary analysis will therefore remain at 0.05.

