## **VIII. MEASURES TO MINIMISE BIAS**

### **VIII-1. Randomisation**

In addition to receiving usual care, eligible patients will be allocated using a central web-based randomisation service (CleanWeb, Telemedicine Technologies, Boulogne Billancourt, France) available at <https://chrub.tentelemed.com>.

The randomisation service will allocate the treatment based on a pre-specified randomization list generated by the data manager. Separate randomisation lists will be used for each patient population. Randomisation will be performed at a 1:1 ratio, blocked (with randomly varying block sizes of two and four) and stratified by centre. Once randomised, patients are irrevocably enrolled in the study, whether or not they are subsequently found to be eligible or actually receive the allocated treatment. As a consequence, patients should be followed until their last visit, until stopping rules apply or death.

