### **X-3. Statistical analysis**

#### **General principles**

All analyses for reports, presentations and publications will be prepared by the coordinating centre at the Research Methods Unit (uMETH) of the Clinical Investigation Centre, University Hospital of Besançon. A more detailed statistical analysis plan will be developed by the investigators whilst still blind to any analyses of aggregated data on study outcomes by treatment allocation.

Although conducted as a single trial with randomisation stratified on the groups of patients (cohort 1 and 2) for operational and logistical reasons, the findings in each cohort are considered as separate trials and are analysed separately.

The final results will be reported according to the recommendations of CONSORT 2010.

All outcomes will be analysed in superiority (two-sided) analyses using simple hypothesis tests. As sensitivity analyses, generalized linear models will be used to account for stratification on the centre. No correction for multiplicity and no hierarchical testing procedures are planned in analysing secondary outcomes. These analyses will therefore be considered as exploratory in nature.

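### The primary Z-test ignores centre and the recorded baseline predictors: it is valid and meets its planned power, but gives up precision that a pre-specified adjusted risk difference would recover

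*Protocol*

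**What the plan says.** VIII-1 sets the allocation: "Randomisation will be performed at a 1:1 ratio, blocked (with randomly varying block sizes of two and four) and stratified by centre", with a separate list for each cohort. X-3 (General principles) sets the rule for analysis: "All outcomes will be analysed in superiority (two-sided) analyses using simple hypothesis tests". For the primary endpoint the same section says "The primary outcome will be analysed using a two-sided Z-test to compare proportions of events in the randomisation groups", and "The risk difference will be provided with its 95% confidence interval".

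Centre appears only in a sensitivity analysis, a logit mixed model with a random centre effect. On other predictors X-3 says "Adjustment for major prognostic factors will be considered depending on the evolution of medical knowledge on the prognosis of patients infected by SARS-Cov-2". It names no covariates, no model and no time of decision.

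VI-4-1 lists the baseline data, including age, high-risk category or comorbidity, symptom onset date and ALAMA risk score. II-3-1 describes advancing age as the main risk factor for hospitalisation and death. VIII-2 accepts that admission can turn on local practice and service availability. The cohorts are analysed separately, so cohort itself needs no adjustment.

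**The concern.** Blocking within centre removes between-centre variation from the treatment contrast, but the standard error of a plain two-sample Z-test still includes it. The interval is then too wide whenever centre is prognostic, and VIII-2 gives reason to think it may be. The planned mixed model does not repair this. It estimates a conditional odds ratio, so it neither narrows the interval of the reported risk difference nor estimates the same quantity.

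Baseline predictors raise the same issue. They are collected anyway, and using them would sharpen the estimate without recruiting anyone. X-2 concedes that the assumed effect may be optimistic and that power may then fall short, so such a gain has some value here.

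**Working it through.** **1. The plan's own figure.** Inputs from X-2: 0.30 versus 0.15, two-sided alpha 0.05, power 90%. With unpooled variance:

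n per arm = (1.960 + 1.282)² × (0.30×0.70 + 0.15×0.85) / 0.15² = 10.507 × 0.3375 / 0.0225 = 157.6, rounded up to **158**.

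This matches X-2 exactly. Power of the unadjusted test is 90.1% at 158 per arm and 92.0% at 170. (The pooled-variance version gives 161 per arm, and 89.5% power at 158.)

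**2. Analytic gain from adjustment.** If centre and covariates explain a share R² of the outcome variance, the variance is multiplied by (1 − R²). The documents give no R², so a range is shown.

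| Assumed R² | Confidence interval width vs unadjusted | Power, 158 per arm | Power, 170 per arm |
|---|---|---|---|
| 0 | 1.000 | 90.1% | 92.0% |
| 0.02 | 0.990 | 90.6% | 92.5% |
| 0.05 | 0.975 | 91.5% | 93.2% |
| 0.10 | 0.949 | 92.8% | 94.4% |
| 0.20 | 0.894 | 95.2% | 96.4% |

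**3. Centre alone, by simulation.** Design: 340 patients, blocks of 2 and 4 within centre. The number of centres and the between-centre log-odds SD are assumptions.

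- 30 centres, no treatment effect: the Z-test rejects in 4.9% of trials at SD 0.4. Separate runs gave 3.5-4.4% at SD 0.7 and 3.0-3.4% at SD 1.0. In one set with 4,000 trials per scenario, the mean standard error exceeded the true SD by 5% at SD 0.7 (0.0495 vs 0.0470) and by 9% at SD 1.0 (0.0494 vs 0.0454).
- 20 centres, SD 0 to 0.6: adjusting for centre changes the standard error by +0.4% to about −3%, and power by at most about 0.6 point.

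Across all the 20-centre null scenarios, with or without a covariate, the Z-test rejected in 3.6% to 5.8% (Monte Carlo error about 0.4 point). The 5.8% scenario also read high for the adjusted analyses of the same data (5.9% and 6.2%), which points to chance and not to a fault of the Z-test.

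**4. One covariate added, by simulation.** 20 centres, centre SD 0.3, 30% vs 15%, 340 patients, 3,000 trials per row. The equivalent gain in patients is 1/(standard error ratio)² − 1.

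| Assumed log-odds per SD | Standard error ratio | Equivalent gain | Power, Z-test | Power, adjusted |
|---|---|---|---|---|
| 0.5 | 0.980 | 1/0.960 − 1 = 4% | 92.1% | 93.1% |
| 0.8 | 0.955 | 1/0.912 − 1 = 10% | 91.6% | 94.1% |
| 1.0 | 0.938 | 1/0.880 − 1 = 14% | 92.1% | 95.1% |

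Separate simulations of the covariate gave 3%, 9% and 14% for the same slopes. Taken together the range is 3-14%. On 340 patients that is 0.03×340 ≈ 10 to 0.14×340 ≈ 48.

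**5. What the interim can carry.** IV-2 puts the interim at 102 patients per cohort. At the planned rates that is 51×0.30 + 51×0.15 ≈ 23 events, too few for a rich covariate model.

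**The case against.** The strongest reply is that nothing is broken. The trial was sized for this very test, the test delivers the stated power, and any departure from 5% is on the conservative side. All of that stands. A reader might infer that planned power is lost or that the test is invalid; step 1 and the null rejection rates support neither.

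The size of the gain also rests on assumed inputs. A centre SD of 1.0 around a 30% rate puts centres one SD either side at about 14% and 54%, which is a wide spread. At low heterogeneity the centre effect is negligible. In cohort 1, eligibility at an age or COVID-age of 70 or more (V-1-1) narrows the range of the main predictor. These points limit the size of the gain but not its direction.

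A reader might also infer from the open sentence on prognostic factors that covariates will be picked on results. The protocol does not support that. X-3 has the detailed analysis plan written blind to outcomes by arm, X-3 ties adjustment to outside medical knowledge, and X-2 gives the interim to an independent statistician and the DSMB. A covariate list may properly sit in the analysis plan, which is not at hand. Two things remain. The protocol itself fixes the unadjusted test as primary. And X-7 allows changes to the analysis plan after discussion between the principal investigator and the methodologist, with no deadline or blinding condition stated.

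**Conclusion.** The point holds as one of efficiency. The primary analysis leaves out the randomisation stratum and the baseline predictors, and its one centre-adjusted companion does not estimate a risk difference. The loss through centre lies between nothing and a standard error about 9% too wide, for between-centre log-odds SDs up to 1.0. The loss through unused covariates is equivalent to about 3-14% of the sample, for a predictor with log-odds 0.5-1.0 per SD, or roughly 1 to 3 points of power at 340 patients. The number of centres, centre SD, slopes and R² are all assumptions, so confidence is high in the direction and moderate in the size. The plan's 90% power and its type I error are not called into question. The change is worth making because it is cheap and keeps the effect measure.

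**What to change.** In X-3, replace the sentence beginning "Adjustment for major prognostic factors will be considered depending on the evolution of medical knowledge" with a pre-specified primary analysis:

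- A risk difference standardised from a logistic model with treatment and a few named baseline covariates. Cohort 1: COVID-age or age (not both, since they overlap) and days from symptom onset. Cohort 2: age, a coarse grouping of the immune deficiencies in V-1-2, and days from symptom onset.
- A variance that accounts for stratification by centre, with a stated rule for pooling small centres.
- The unadjusted Z-test kept as a sensitivity analysis.
- At the interim, either the simple Z statistic or a reduced covariate set. Confirm that the promising-zone limits in X-2 (Z of 1.07 and 1.66) and the type I error argument in X-3, which refers to the conventional Wald statistic, still hold for the statistic chosen.

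The cost is revised wording, modest programming, a model-based primary estimate, and the re-check of the interim rules. The sample size need not change.
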